**Randomization:**

Randomization for this study will be done by the Investigational Drug Services (IDS) using www.randomization .com. Randomization will be 1:1 (metformin : placebo) and will be blocked for every 10 subjects. Pharmacy will maintain blinding information and PI will contact IDS for emergency unblinding. IDS is available 24 hours a day and 7 days of the week via pager. Call schedule is available on OurNet.

e. How long will each subject be enrolled in the study?

Twelve months.

f. Provide a *brief* overview of what participation in the study will mean to each participant in terms of what he/she will experience. Describe in order, each procedure, how long each procedure will take and how often each procedure will be performed. Include doses & route of administration of any drugs and whether the procedure or drugs would **always**, **sometimes** or **never** be required as part of the subject’s standard of care.

Methods and assessments:

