**Inclusion criteria:**

1. **General inclusion criteria**
2. Ten to 18 years of age.
3. Pubertal (Tanner stages 2-5, by examination).
4. Hemoglobin A1c level of > 8.0% in the 6 months prior to enrollment.
5. All subjects must have access to a computer.
6. **Specific inclusion criteria: [Subjects could have either #1, or #2].**
7. Subjects with clinical and biochemical features of T2DM of > 6mo duration who also have positive T1DM antibodies
   1. Clinical features: acanthosis nigricans, BMI >85%
   2. Biochemical: evidence of insulin resistance at diagnosis
      1. fasting insulin >27 uIU/mL(normal range 6-27) at a fasting blood glucose of ≥ 126 mg/dL, or
      2. fasting c-peptide level of > 7.1 ng/mL (normal range 0.9 – 7.1), or
      3. Homeostasis model of insulin resistance of >3.16
8. Patients with T1DM of > one yr duration with BMI >85%
   1. Presentation with ketoacidosis at diagnosis
   2. C-peptide <0.9 ng/mL (normal range 0.9 – 7.1),or (insulin < 6 uIU/mL) (NR 6-27) at diagnosis (when blood glucose is ≥ 126 mg/dL)
   3. Can be antibody positive or negative
   4. Increased insulin requirement (>2 Units/kg/day)

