**Sample size calculation and Statistical Analysis:**

All patients will undergo a 3-month run in phase, during which they will be on detemir and aspart only, with no added metformin or placebo. (Please see a detailed explanation of the run-in phase under Trial Design above). At the end of the run-in period,patients will be assigned to one of the two treatment groups (placebo or metformin) using a random number generation process. Placebo and metformin will be offered in similar form, to ensure participants are blinded to their assignment. Group assignment will be established by a research pharmacist with no direct participation in the study; and principal investigator will not be informed of what group each individual is assigned to.

The primary outcome chosen to measure the impact of metformin on the management of “double diabetes” children is their level of glycosylated hemoglobin (Hb A1c, measured as a %). The secondary outcomes are: a) blood pressure (mmHg), b) waist circumference (cm), c) body mass index (BMI, kg/m2), d) lipid profile (LDL and HDL cholesterol and triglycerides (mg/dL)), e) ), leptin (ng/dL), and f) 25-hydroxyvitamin D (ng/mL), g) adiponectin (µg/mL ), and total daily dose of insulin.

All outcomes will be measured on an ongoing basis, at the beginning of the trial, and then at 3 months intervals during the entire study period. The intervention arm of the study will last 9 months. **Sample size calculations** are based on the simple comparison of paired means. Using a confidence level of 95% (Z (1-α/2) = 1.96 for a two-tailed test) and a statistical power of 80% (Z (1-β) = 0.84), calculated group sizes are 29 individuals for each arm of the trial. This number is based on the assumptions that 1) supplementing the treat-to-target protocol with metformin will decrease the Hb A1c level by at least 1.5 percent units, and 2) the standard deviation for Hb A1c levels in obese adolescents is estimated to be 2. Because of the duration of the study, and the possibility of loss to follow-up, a 25% attrition allowance has been made on the ‘n’ of 58, bringing the total number of participants to 74. This is a conservative approach to the sample size calculation, because the repeated measurements will, by construction, improve the power of the study, improving its ability to capture outcomes with more variability than expected.

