**Subject Replacement:** To ensure adequate sample size to reach significance according to our power calculations, we will oversample by 25% for each arm of the study. This will enable adequate numbers despite predicted study attrition.

**Statistical analyses** will be conducted so as to capture both the absolute changes in serum values for the proposed outcomes, as well as “time-to-event” information allowing us to compare the 2 groups with maximum efficiency.

1) **H1A**: Metformin supplementation of treat-to-target insulin regimen of diabetes care will have an influence on levels of HbA1c over time.

Mean levels of HbA1c will be computed at each time point, applying arcsine transformation to approximate Normality. 95% Confidence Intervals (95% CI) will be constructed around these estimates. All results will be graphed for visual appreciation of possible trends. Consecutive HbA1c levels for patients with and without metformin will be compared using repeated-measures Analysis of variance (ANOVA). Analyses of Covariance will be modeled to account for possible confounding due to gender and age. Similar analyses will be applied to the FPG levels, using the logarithmic transformation instead.

2) **H1B**: Patients randomized to adjunctive metformin therapy will achieve a greater reduction in HbA1c and fasting plasma glucose than those on placebo.

Adjunctive metformin and placebo groups will also be compared using both a logistic model and an actuarial survival model for “time-to-event”, where the event of interest is the decrease of the HbA1c level to 8% or less, as the biological cutoff below which serum glucose levels are considered stabilized. Similar analyses will be applied to FPG levels.

3) **H1C**: Metformin supplementation of treat-to-target regimen of diabetes care will have a measurable influence on blood pressure, waist circumference, body mass index, lipid profile, leptin, adiponectin, and 25-hydroxyvitamin D.

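### Entry route (type 2 with antibodies, or type 1 with high BMI) is known before randomisation but is used neither to stratify allocation nor as a factor in the HbA1c and secondary models; the gain forgone is small to modest

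*Protocol*

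**What the plan says.** Protocol section 4b (Inclusion criteria) opens two routes into the trial: "Subjects could have either #1, or #2". The first is type 2 diabetes of more than 6 months with type 1 antibodies and evidence of insulin resistance at diagnosis, for which one of three alternatives is "fasting c-peptide level of > 7.1 ng/mL". The second is type 1 diabetes of more than one year with BMI above 85%; its listed features include "C-peptide <0.9 ng/mL" at diagnosis, or low insulin, and an increased insulin requirement.

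Section 4d (Randomization), repeated in the trial design text of section 4a, fixes the allocation: "Randomization will be 1:1 (metformin : placebo) and will be blocked for every 10 subjects". No stratification factor appears in either place.

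Section 4c states the adjustment under H1A for HbA1c, and again under H1C for the secondary outcomes: "Analyses of Covariance will be modeled to account for possible confounding due to gender and age". The logistic and survival models under H1B name no covariates. Entry route is not mentioned in any allocation or analysis text.

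**The concern.** Entry route is an eligibility criterion, so it is recorded for every patient before allocation. The protocol gives some reason to think it is prognostic. Its background section reports HbA1c of 9.5% or more in 17% of youth with type 1 and 27% with type 2. It also calls the metformin reports in type 1 adolescents conflicting, while trials in type 2 adolescents improved fasting glucose.

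The number entering by the type 2 route is not planned. The recruitment count under the Treat to Target Regimen heading covers only type 1 patients, and exclusion criterion 12 removes current metformin users. A small group allocated from a single list can split unevenly. If its HbA1c course differs, the observed arm difference moves with the split, and any route difference left out of the model stays in the error term. The protocol fixes both the allocation scheme and the covariates for these models, so this goes beyond detail normally left to a statistical analysis plan.

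**Working it through.** **Inputs from section 4c.** Two-sided 5% level, power 80%, effect 1.5 HbA1c points, SD 2, 29 per arm, 74 randomised (taken here as 37 per arm).

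**Assumptions, because the protocol gives no figure.** K = 8 to 22 of the 74 enter by the type 2 route, and mean HbA1c at follow-up differs between routes by d = 0.5, 1 or 2 points.

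**Step 1: the plan's own figure.** For two independent means, n per arm = 2 × (2 × 2.80 / 1.5)² = 27.9. The two-sample t-test gives 28.9, so 29, which matches. Power at 29 per arm by the t-test is 80.1%. (The text speaks of paired means, but 29 is the independent-groups figure.)

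**Step 2: chance imbalance.** If k of the K type 2 route patients fall in one arm, the arms differ in route share by |2k − K| / 37, with k hypergeometric (74, K, 37). Simulating the actual blocks of 10 gives almost the same chances of a 2:1 split, so the existing blocking does not protect against imbalance on route.

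**Step 3: shift in an unadjusted follow-up difference.** Shift = imbalance in share × d.

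**Step 4: precision.** With p = K/74, route explains p(1 − p)d²/4 of the variance, where 4 is the planned SD squared. The residual SD is 2 × √(1 − that share). Power is the t-test at effect 1.5 and 29 per arm.

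| K | Chance of 2:1 split or worse | Mean absolute imbalance (points of share) | Mean shift, d = 1 | Mean shift, d = 2 | Power, d = 0.5 | Power, d = 1 | Power, d = 2 |
|---|---|---|---|---|---|---|---|
| 8 | 26% | 5.6 | 0.06 | 0.11 | 80.4% | 81.1% | 84% |
| 15 | 25% | 7.6 | 0.08 | 0.15 | 80.5% | 81.7% | 87% |
| 22 | 7% | 8.4 | 0.08 | 0.17 | 80.7% | 82.2% | 88% |

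For K = 11 the chance of a 2:1 split or worse is 19%; its imbalance and power lie between the first two rows.

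Example for K = 8, d = 1: p = 0.108, p(1 − p) = 0.096, variance share 0.096 / 4 = 2.4%, residual SD 1.98, power 81.1%. Across K = 8 to 22, the variance share is 0.6-1.3% for d = 0.5, 2.4-5.2% for d = 1 and 9.6-20.9% for d = 2.

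**Step 5: an unfavourable split.** With K = 15, a 10:5 split is (10 − 5)/37 = 13.5 points of share and moves the estimate by 0.14 (d = 1) to 0.27 (d = 2). A split this uneven or worse has a 25% chance.

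**Yardsticks.** The standard error of the arm difference is 2 × √(2/37) = 0.46 with all 74, or 2 × √(2/29) = 0.53 with 58. The planned effect is 1.5. The two randomised trials cited in the background each show an arm difference of about 0.6 (falls of 0.9 against 0.3; −0.3 against +0.3).

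**The case against.** The best defence is that this is a design preference and not an error. Unstratified blocked randomisation is valid, and the standard error of the unadjusted comparison already allows for chance imbalance in route. That stands: a reader might infer that the trial is biased, and it is not, in expectation.

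A reader might also infer that the routes are opposite in insulin reserve. The criteria do not support this. The cut-offs apply at diagnosis, months or years before entry. A HOMA-IR above 3.16 alone can meet the biochemical criterion of the type 2 route, with no need for a C-peptide above 7.1. The type 1 route itself lists a marker of insulin resistance, a requirement above 2 units/kg/day. Both routes call for high BMI, and all patients share the HbA1c entry threshold, the run-in insulins and the titration scheme.

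The size is open to challenge too. No passage gives an HbA1c gap between routes. A gap of 1 to 2 points is half to one full planned SD, and at 0.5 points the power gain is under one percentage point. The HbA1c analysis uses repeated measures from baseline, and H1B concerns reduction. Comparing change over time takes out a stable difference in level between routes, leaving differences in trajectory or in response to metformin. If the type 2 group is very small, uneven splits are more likely but matter less: with 5 patients, the mean imbalance is 4.9 points of share, or 0.05 HbA1c points at d = 1.

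These points limit the weight of the finding. They do not remove it: the factor is already recorded, the protocol accepts covariate adjustment in principle, and using route costs almost nothing.

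**Conclusion.** The point holds as a modest, low-cost improvement in efficiency. Entry route is left out of the allocation and out of the named covariates for the HbA1c and secondary models. With 8 to 22 of 74 patients in the type 2 route, a typical chance imbalance shifts an unadjusted follow-up HbA1c difference by 0.06-0.08 points for a 1-point gap and 0.11-0.17 for a 2-point gap, which is well inside one standard error. Use of baseline would make it smaller. The power gain runs from under one percentage point (gap 0.5) to about eight (gap 2, 22 patients). Route share and gap are both assumptions.

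It would go too far to say that every between-arm model ignores route. The logistic and survival models name no covariates at all, and a statistical analysis plan may fill that silence. Nor does the general statement of the problem promise a separate answer for each route: it describes who is enrolled.

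**What to change.** In section 4c, under H1A and H1C, add entry route (type 2 with antibodies, or type 1 with high BMI) as a fixed factor alongside gender and age in the HbA1c and secondary-outcome models.

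If randomisation has not begun, also amend section 4d and the matching text in section 4a to stratify the list by entry route, with blocks smaller than 10 (for example 4). A stratum of eight patients would not fill one block of 10. If randomisation has begun, make the model change alone and date it before any unblinded outcome data are seen by those doing the analysis.

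The cost is one degree of freedom and a second list for the pharmacy to hold, with no added patients, visits or data. Smaller blocks are somewhat easier to predict, but the pharmacy keeps the list and physicians and patients are blinded. Showing the arm difference by route is optional and should be descriptive only, because the smaller group may have about four patients per arm.

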**Visit Procedures (See Table 1)**

We will keep a subject screening log and a subject enrollment log.

In case of any premature discontinuation of the trial, we will make every effort to call in the subject for a last visit. We will specify primary reason (adverse event, non-compliance with protocol or other) for discontinuation in the CRF. If the subject is not able to attend, we will complete the End of Trial Form and fill in the Drug Accountability Form.

**Protocol**:

This research study involves 6 visits: two screening visits and 4 study visits. Subjects who meet the inclusion criteria will be invited to enroll in the study. Parental **consent** will be obtained before any subject is enrolled in the study. In addition to the parental consent, minors from age 10 to 15 years will read and sign an **assent form**. Older adolescents (16 and 17) will read and sign the same consent form as their parents signed. This ensures that all participants fully understand the requirements of the study and are competent to participate in it.Subjects will undergo a 3-month **run-in period** to screen for complications, to update patient education, and to assess subject’s compliance with study protocol. Patients will be placed on detemir and aspart with no adjunctive metformin or placebo during the run-in period. (Please see a detailed explanation of the run-in phase under Trial Design above). All participants will be instructed on the treat-to-target regimen and be given a **summary sheet** to familiarize themselves with the regimen. Treat-to-target regimen will only commence at the end of the run-in phase.

**1. VISIT I: START OF THE RUN-IN PERIOD AND SCREENING VISIT AT -3 MO**

*History:* To ensure eligibility for the study, we will take a detailed history of subject’s medical condition. This history will focus on patient’s current medical diagnosis, past medical and birth history, social history. We will document any family history of type 1 or type 2 diabetes, obesity, and related comorbidities. We will also document subject’s medications, supplements, diet and exercise plan.

*Physical Examination:* All participants will undergo a detailed physical examination at baseline, and at 3 month intervals throughout the duration of the study. The aims of the physical examination will be (1) to rule out medical conditions that could present with obesity, such as Cushing’s syndrome, severe hypothyroidism, and Prader Willi syndrome; (2) to identify complications of diabetes; (3) to identify dermatologic features associated with insulin resistance, such as acanthosis nigricans, and skin tags; (4) to document appropriate Tanner stages in all participants.

*Screening Laboratory Test:* All participants will undergo a screening study consisting of serum creatinine, liver function tests, thyroid function tests, and celiac antibody panel. Subjects with abnormal liver or kidney function tests will not be enrolled in the study. Subjects with abnormal thyroid function test will be treated and will be enrolled when euthyroid. Subjects with abnormal celiac antibody panel will be enrolled after a consultation with a gastroenterologist.

*Urine Sample:* A spot urine sample will be collected for microalbumin and creatinine at baseline. Urine pregnancy test will be obtained on all female participants and will be repeated at baseline, +3mo, and + 6mo.

*Run-in phase:* All participants will be transitioned to detemir and aspart, without instituting treat-to-target regimen, or adding metformin or placebo. (Please see a detailed explanation of the run-in phase under Trial Design above).

**2. VISIT II: REVIEW OF RUN-IN PERIOD GLYCEMIA AND NUTRITION COUNSELING AT -2 MO.**

All participants will return to the clinic one month after the start of the run-in phase for a brief physical examination, review of glucose data, and insulin dose adjustments. We will also review the protocol for patient-directed, treat-to-target regimen with the families.

*Nutrition Counseling*: All subjects will undergo nutrition counseling by a board certified dietician at -2, 0, +3, and at +6 months.

**3. VISIT III: BASELINE INTERVENTION STUDY VISIT AT O MO**

Following the screening study, qualified subjects will return to the Children’s Diabetes Service in the morning, after an overnight fast for initial intervention study blood draw. Anthropometric measurements: height, weight, waist circumference will be obtained. Vital signs and fasting glucose level will be checked. A venous catheter will be inserted in the antecubital fossa and blood sample will be drawn for fasting lipids, leptin, and 25-hydroxyvitamin D at baseline.

*Vital Signs:* Blood pressure and pulse will be measured using an electronic sphygmomanometer.

*Physical Examination:* Weight, height and waist circumference will be measured in all participants at baseline, 3 months and 6 months. Weight will be measured using an electronic scale with patient donning under-garments and a hospital gown. Values will be expressed to the nearest 0.1 kg. Height will be measured using a wall-mounted Harpenden stadiometer. Waist circumference will be measured at the level of the umbilicus, using a standard measuring tape. All measurements will be done in triplicates and the average taken. We will derive body mass index from the weight and height data.

*Blood samples:* At baseline, following an overnight fast, we will draw fasting blood samples for the following laboratory tests: lipid profile, leptin, adiponectin, hepatic function tests, serum creatinine, and 25-hydroxyvitamin D. These analytes will be redrawn at 3, 6 and 9 months. Only 2 teaspoons of blood will be drawn for these tests at each time point. All samples will be spun upon collection using a centrifuge and the serum collected and stored at -70 degrees until assay. Whole blood samples will be collected for HbA1c estimation.

Urine test: Urine pregnancy test will be obtained on all female participants and will be repeated at +3mo, and + 6mo.

**Procedure**

Following the blood draw, each subject will be started on a patient-directed, treat-to-target insulin regimen. All participants will be on multiple daily injections (MDI) consisting of once daily injection of long acting insulin analog, detemir, meal time insulin boluses with aspart, and a correction factor for insulin to ensure euglycemia between meals. All insulins will be administered using a flexpen device. For this study we will confirm the adequacy of each aspect of therapy by an ongoing monitoring system as described by Bode et al[59], and summarized below. We will use a ‘teach back’ protocol to ensure that patients understand the bolus insulin adjustment and correction factor plan.

Our goal for the participants is to maintain their blood glucose levels as shown below in the Table 2.

**Table 2. Summary of Expected Blood Glucose Levels at Different Times of the Day**

| Time | Before breakfast | Before lunch or dinner | Before bedtime | 2 hours after a meal | At 3AM |
| --- | --- | --- | --- | --- | --- |
| Expected Glucose level (mg/dL) | 90-120 | 80-130 | greater than 100 | less than 220 | greater than 100 |

**A. Bolus insulin dose adjustment plan:** All participants will be placed on treat-to-target regimen plus either metformin or placebo as described below. The insulin boluses for meals will be calculated from an insulin to carbohydrate ratio that would be predetermined by the endocrinology team for each patient. We will strive to maintain a basal : bolus insulin ratio of 1:1, i.e., each component will constitute 50% of the total daily dose of insulin. Our goal is to maintain a premeal blood glucose level of 90-130 mg/dL. To adjust premeal bolus doses, we will focus on the pattern of blood glucose levels before lunch, dinner, and bedtime. If the blood glucose levels at the same time of day (e.g., before dinner) are high **two days** in a row, we will increase the preceding premeal (e.g., before lunch) bolus by 10 percent. Conversely, we will decrease a preceding premeal bolus by 10% if a **single** low blood glucose is obtained before a meal. Changing this bolus dose the very next day will prevent a recurrence of hypoglycemia and thereby protect against the establishment of reduced hypoglycemic awareness[60]

**B. The correction factor or supplemental insulin dose adjustment plan:** The correction factor or supplemental insulin is the amount of fast-acting insulin that is added or subtracted from the insulin boluses to maintain euglycemia 2 hours after a meal as shown below in Table 3. The formula for the correction factor is (BG-X)/ISF, where BG is current blood glucose, X is ideal blood glucose for the patient, and ISF is insulin sensitivity factor. ISF will be calculated using the 1500 Rule, i.e., 1500 divided by the total daily dose of insulin. Our goal is to maintain a 2-hour post-prandial glucose level of <180 mg/L. To analyze the accuracy of the supplemental doses, we will look at every high blood glucose level and the level immediately following it. Specifically, if every high blood glucose level is followed by one in the target range, this indicates that the patient’s supplemental dose is correct. However, if most high blood glucose levels are followed by hypoglycemic levels, then the supplemental dose is too high. Conversely, if most high levels are followed by another high level, then the supplemental dose is too low. We will advise the participant to decrease or increase the sensitivity factor in the supplemental formula as needed to achieve the desired change in the blood glucose level as shown in Table 3.

